### Recruitment

We aim to test the AMT intervention on a sample of approximately 250 frontline police officers in rolling cohorts of 10-15 participants (half AMT, half waitlist control) from geographically representative police services across Canada. A power analysis was conducted using G*Power software [43] and found that a minimum total sample size of 128 participants was required (effect size f=0.25, α=.05, power=0.80, number of groups=2, number of repeated measures=2). However, we plan to oversample officers by sex and mitigate possible attrition based on the principal investigator’s previous experience with conducting longitudinal research on police officers [31-33]. A small laboratory-based prepilot sample (n=10) will test equipment reliability, accuracy, and integration of HR monitors with HRVBF and learning management system (LMS) platforms. An initial pilot cohort 1 (n=30) will then test the AMT intervention in the population of interest (ie, law enforcement officers) using a combined laboratory-remote paradigm to validate the implementation of study procedures. These participants will also be invited to participate in a poststudy focus group as per the study protocol (see iKT Focus Groups in Procedures) to optimize the intervention (ie, content and delivery) and overall study procedures to provide stakeholder- and user-informed feedback. When all user feedback has been incorporated, all subsequent participants will be tested fully remotely and in accordance with the randomized control trial procedures and group allocation.

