### Outcomes

In accordance with our hypotheses, PTSI (H1) will be measured by the PHQ-8, GAD-7, DASS-42, PCL-5, AUDIT, PSS, CBI, and self-reported stress visual analog scale. Self-reported resilience and well-being (H2) will be measured by the Brief COPE, RSA-33, BRS, WBSI, PTQ, UB-PSWQ, and UB-RRS. Functional wellness capacity and occupational stress will be measured by the SDS, GHPS, COVID-19 HRSI, WHODAS 2.0, PSQ, and LEAPS. Sex will be measured by self-reported sex at birth (male, female, or other); gender is measured by self-identification as male, female, nonbinary, or other (with the option to self-report) or “prefer not to disclose.” Sex and gender-related experiences will be measured by the WGDS and GEQ (H3 and H7). Changes in resting HRV (H4) will be measured by time and frequency domain parameters based on data collected from the wearable HR monitors (eg, high- and low-frequency HRV, low- or high- frequency ratio, and the Root Mean Square of Successive Differences, [RMSSD]) as recommended in the standards of practice for HRV analysis [17]. RSA (H5) will be measured by obtaining respiratory frequency. Greater power at the respiratory frequency indicates a higher level of RSA and will be analyzed using the gold standard HRV analysis program, Kubios [92]. Recovery from acute stress (H6) will be measured following completion of the web-based PASAT and emotional Stroop Tasks. Acute stress recovery will be assessed via a time-domain measure of HRV (RMSSD) [17].

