To test the effectiveness of the AMT intervention on improving biological indicators of resilience, prepost analyses of resting HRV parameters (H4), RSA (H5), and recovery from acute stress (H6) will be separately assessed using repeated measures ANCOVAs with sex, gender (H7), age, years of service, and geographic service region as covariates. To determine which factors significantly predict greater changes in biological outcome measures, hierarchical linear regression analyses will be undertaken with self-reported measures and demographic variables entered as predictors in the models. We will also compare weekly changes in HRV and RSA as measured during AMT module exercises with repeated measures ANCOVAs. A main effects analysis of the “time” variable will explore the potential incremental benefit of AMT training and identify at what point during the 6-week intervention significant biological changes occur. Computational approaches to analyzing and visualizing biological indices of resilience will be led by CM, including integration of cardiac (eg, HRV) and respiratory (eg, RSA) rhythms to elucidate patterns of desynchronization before, during, and following AMT.

To explore sex and gender-based contributions to self-report (H3) and objective indices (H7) of PTSI and resilience, the above analyses will include sex and gender as covariates or predictor variables with sex-stratified samples. These findings will clarify any sex-related differences in baseline and postintervention rates of PTSI and resilience among law enforcement officers and whether there are any sex-related differences in the magnitude of treatment effects (H3). Moderated regression analyses will test whether the AMT intervention affects the relationship between sex and PTSI symptoms and resilience. Multiple comparisons will be adjusted with Bonferroni corrections, where applicable.

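### Bonferroni is a valid multiplicity correction here, but Holm step-down gives the same familywise error control and never rejects less: a small, nearly free efficiency gain

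*Protocol article*

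**What the plan says.** Data Security and Analyses closes its paragraph on sex and gender with "Multiple comparisons will be adjusted with Bonferroni corrections, where applicable". This is the article's only multiplicity statement. It names the method but not the family of tests.

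Under Outcomes, "PTSI (H1) will be measured by the PHQ-8, GAD-7, DASS-42, PCL-5, AUDIT, PSS, CBI, and self-reported stress visual analog scale", which is 8 measures. The same section lists 7 measures of resilience and well-being for H2. Data Security and Analyses tests the H1 and H2 measures in separate repeated measures ANCOVAs, and mentions no adjustment at that place.

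Under Recruitment, the power analysis uses "effect size f=0.25, α=.05, power=0.80, number of groups=2, number of repeated measures=2" and concludes that "a minimum total sample size of 128 participants was required". The plan is to recruit "a sample of approximately 250 frontline police officers", "half AMT, half waitlist control". The excess over 128 is explained by "we plan to oversample officers by sex and mitigate possible attrition", without a dropout rate.

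**The concern.** Once a family of m tests is chosen, Bonferroni compares every p-value with 0.05/m. Holm compares the smallest with 0.05/m, the next with 0.05/(m−1), and so on, stopping at the first failure. Each Holm threshold is at least as large as Bonferroni's, and both procedures hold the familywise error at 0.05 under any dependence. Naming Bonferroni therefore gives up some power with no gain in error control.

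What is at stake is how many individual scales can be reported as improved once at least one has been. H1 and H2 each rest on a battery of 7 or 8 scales tested separately, so a reader will look at the individual scales. Whether any scale is declared improved is not at stake: the first Holm step is the Bonferroni threshold.

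**Working it through.** **Inputs from the article.** Effect size f=0.25; α=0.05; power 0.80; minimum total N=128; planned N about 250; allocation 1:1; 8 H1 measures.

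**Assumptions, because the article gives none.** The 8 H1 scales form one family; the correlation between scales is 0.5 (0.3 and 0.7 also tried); the effect is equal on every scale where it is real; the number of real effects is 8, 4 or 2. A smaller effect, d=0.36, is tried as a sensitivity case. Participants are treated as independent and no attrition is taken off.

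**1. The article's own figure.** For two groups, noncentral F with λ = f²N and df = 1 and N−2. At N=128, λ = 0.0625 × 128 = 8.0 and power = 0.801. The minimum of 128 reproduces, with α undivided. For two equal groups d = 2f = 0.5.

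**2. Bonferroni at the planned size.** With α = 0.05/8 = 0.00625, the same formula gives power 0.883 at N=250 and 0.521 at N=128; 80% power needs N=210. With α = 0.05/7 for the 7 H2 scales, power at N=250 is 0.891 and 80% needs N=204. With all 15 scales in one family (α = 0.05/15) the figures are 0.837 and N=234. At 250 analysed, Bonferroni therefore stays above the 80% target in all three families.

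**3. Normal approximation used in the comparison.** The noncentrality per scale is d√(N/4). The two-sided Bonferroni critical value at 0.00625 is 2.734.
- N=250, d=0.5: 0.5 × √62.5 = 3.953; power = Φ(3.953 − 2.734) = 0.888.
- N=128, d=0.5: 0.5 × √32 = 2.828; power = Φ(2.828 − 2.734) = 0.537.
- N=250, d=0.36: 0.36 × √62.5 = 2.846; power = Φ(2.846 − 2.734) = 0.544.

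**4. Bonferroni against Holm.** Simulated sets of 8 equally correlated z-statistics, correlation 0.5, 100,000 runs per row. Power is the average over the scales with a real effect.

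| N | d | Real effects | Bonferroni | Holm | Gain (points) |
|---|---|---|---|---|---|
| 250 | 0.5 | 8 of 8 | 88.9% | 95.3% | 6.4 |
| 250 | 0.5 | 4 of 8 | 89.0% | 91.1% | 2.1 |
| 250 | 0.5 | 2 of 8 | 88.9% | 89.5% | 0.6 |
| 128 | 0.5 | 8 of 8 | 53.8% | 64.6% | 10.8 |
| 128 | 0.5 | 4 of 8 | 53.7% | 56.8% | 3.1 |
| 250 | 0.36 | 8 of 8 | 54.3% | 65.3% | 11.0 |
| 250 | 0.36 | 4 of 8 | 54.7% | 57.8% | 3.1 |
| 250 | 0.36 | 2 of 8 | 54.7% | 55.6% | 0.9 |

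The chance of at least one rejection is the same for both methods in every row: for example 99.7% at N=250, d=0.5 and 91.0% at N=128, d=0.5, with all 8 real. With no real effect, the familywise error is the same for both, about 4% at correlation 0.5.

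**5. Sensitivity to correlation.** At N=250, d=0.36 with all 8 real, the gain is 11.4 points at correlation 0.3 (54.5% against 65.9%) and 10.2 at 0.7 (54.0% against 64.2%). Correlation matters little to the gain; the number of real effects and the level of power drive it.

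**The case against.** The strongest case against is that nothing is wrong. Bonferroni is valid under any dependence, is a common conservative choice, and gives simultaneous confidence intervals that match its tests. At N=250 and the article's own effect size it keeps more than 80% power for families of 7, 8 or 15. All of this stands, and it is why the point concerns efficiency only. It does not remove the point, because Holm dominates for whatever family is chosen, and the article announces no simultaneous intervals that would favour Bonferroni.

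Three stronger readings are tempting, and the article does not support them.
- A reader might infer that real effects on the H1 and H2 scales will be lost to Bonferroni. The article never makes those scales a Bonferroni family: the sentence sits in the paragraph on sex and gender and is limited to where it applies.
- A reader might infer that the number of significant scales decides H1 or H2. No such rule is stated. The chance of declaring all 8 does differ more sharply (60% against 87% at N=250, d=0.5, all 8 real), but the article sets no such criterion.
- A reader might infer that the overlap between scales is itself an argument for Holm. Holm does not use correlation either; only a resampling method such as step-down maxT does.

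Attrition cuts the other way. If 200 were analysed (an assumption), with d=0.5, correlation 0.5 and all 8 effects real, power per scale would be 79% with Bonferroni and 88% with Holm.

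**Conclusion.** The point holds as a low-priority efficiency gain. Bonferroni is valid, and Holm offers the same familywise error control and never fewer rejections. At the article's own N=250 and d=0.5, the gain in average power per scale is about 6 points if all 8 effects are real, 2 if 4 are, and under 1 if 2 are. It reaches about 11 points only when every effect is real and power per scale is near 54%: N=128 with d=0.5, or N=250 with the assumed d=0.36. These figures rest on the assumed 8-scale family, equal effects and correlation 0.5. The dominance of Holm rests on none of them. The change does not define the family, which the quoted sentence leaves open.

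**What to change.** In Data Security and Analyses, replace the reference to Bonferroni corrections with Holm step-down, applied within each hypothesis family. If the correlation between scales is to be used, step-down maxT by re-randomisation is an option. In the all-real cases with an average power of about 65% under Holm, a separate simulation put it another 2 to 3 points higher (68% against 66% at N=250, d=0.36; 67% against 64% at N=128, d=0.5).

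The cost is one line of wording, with no change to design, sample size or data collection, and no rejection that Bonferroni would make is lost. The downside is that simultaneous confidence intervals matching Holm are less direct. Ordinary 95% intervals can be reported beside the adjusted p-values, labelled as unadjusted, since they can disagree with the adjusted tests.

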## Results

The study received notice of funding acceptance in March 2020. In February 2021, ethics approval was obtained from the University of Toronto’s Social Sciences, Humanities, and Education Research Ethics Board (Protocol #39478) and was renewed in February 2023. Phase 1 of the study (AMT Development) was completed in December 2022. Participant recruitment for phase 2 began with the pilot cohort in February 2023 via advertisements through partnering stakeholders (see Recruitment section). As of April 2023, 7 pilot participants were actively registered for the AMT intervention. Knowledge dissemination for phase 1 was completed in March 2023 at an annual meeting of the public safety wellness team grant holders and is planned for 1 scientific (May 2023) and 1 practitioner (October 2023) conference. iKT focus groups will take place following the completion of each sufficient cohort (see the iKT Focus Groups section above).

## Discussion

Based on the extant and precedent literature, we predict that the stated hypotheses will be confirmed following the execution of the proposed protocol. Specifically, we anticipate significant reductions in PTSI symptoms and improvements in physiological indicators of health and resilience following the completion of the 6-week web-based AMT intervention. We also anticipate sex- and gender-based differences in pre- and postintervention outcomes, such that self-identified females will report higher PTSI symptoms and lower resilience at baseline and a greater reduction of PTSI symptoms and greater increase in resilience at follow-up than self-identified males. The direction and magnitude of sex- and gender-based differences in physiological outcomes are not currently specified, given the novelty of these analyses. Insights derived from iKT focus groups will supplement the quantitative sex- and gender-based analyses (H3 and H7).

AMT fills an existing gap in the applied research literature supporting evidence-informed prevention and intervention programs for PSP exposed to PTSI, such that AMT aims to measure and strengthen objective biological resilience [12]. Specifically, we are developing a tool that integrates wearable technology, real-time app-based visualized biofeedback tailored to an individual’s biological rhythms, and confidential web-based resources that meet the needs of accessibility and availability expressed by PSP organizations and governmental agencies [16]. Furthermore, our project addresses population-specific needs, including stigma reduction and gendered perspectives on occupational and organizational stress from female officers. By delivering our program on an LMS platform that can be accessed remotely in the privacy of one’s own home, we are providing officers with a secure and accessible wellness promotion intervention and resources that they might not otherwise seek out. This project will also contribute substantial new knowledge to the scarce literature about how sex and gender are related to biological indicators of PTSI and resilience (ie, HRV and RSA). Specifically, analyses will reveal the directionality and strength of interactions between sex and gender and physiological resilience outcomes (eg, what was thought to be sex-based differences in HRV may be related to gender norms and gender stress; see [95]). Our study provides a well-powered design to sufficiently address the persistent knowledge gap in this area.

AMT techniques have previously garnered high “buy-in” from participating police officers because the intervention provides tangible, real-time, biological evidence of occupational and health improvement from the very first HRVBF session [31-34]. Buy-in is further promoted by potentially relieving some symptoms early on without having to wait until the end of the intervention. Further, AMT directs focus on more “physical” rather than “psychological” symptoms to reduce the association of PTSI with potential weakness or occupational inadequacy among police, which has been previously noted [33,96].

Pending significant results, AMT can be delivered alone or in tandem with other psychotherapeutic treatments, such as cognitive behavioral therapy, to provide PSP services with an attractive suite of resilience and wellness capacity interventions that reduce PTSI symptoms and save operating costs (eg, maintenance fees for multiple participant licenses) [97]. The intervention, if found to be effective, can be implemented on a larger scale with affordable, commercially available wearable technology (eg, FitBit and Apple iWatch) and apps (eg, HRV Trace and HRV Train) [98].

Rapid and direct knowledge dissemination to various stakeholders (eg, police organizations, unions, and professional and nonprofit first responder organizations such as The Haven, Badge of Life Canada, Ontario Women in Law Enforcement, and Wounded Warrior) will be facilitated by knowledge users’ (MLV and PS) capacities as retired PSP, board members, and English-French bilingual contributors to police periodicals including “The Blue Line.” In addition to this protocol, several research articles will be prepared based on the planned objectives and analyses identified above. High-impact peer-reviewed journals in relevant fields (eg, Psychophysiology, International Journal of Environmental Research and Public Health, and Policing) that provide open access options will be prioritized. Research findings on the pilot (n=30) and complete data sets (n=250) will be disseminated at scientific (Association for Applied Psychophysiology and Biofeedback, Society for Psychophysiological Research) and applied practitioner conferences (Law Enforcement and Public Health, Canadian Institute for Military and Veteran Health Research, Canadian Association of Chiefs of Police, Canadian Association of Police Educators) to distribute new knowledge generated to the widest audience possible.

## Appendix

Multimedia Appendix 1 Peer review from the Canadian Institutes of Health Research (CIHR).

## Abbreviations

AMT: autonomic modulation training
ANCOVA: analysis of covariance
ANS: autonomic nervous system
AUDIT: Alcohol Use Disorder Identification Test
BRS: Brief Resilience Scale
CBI: Copenhagen Burnout Inventory
COVID-19 HRSI: COVID-19 adapted version of the Holmes Rahe Stress Inventory
DASS-42: Depression and Anxiety Stress Scale-42 Item
GAD-7: General Anxiety Disorder Scale-7 Item
GEQ: Gender Experiences Questionnaire
GHPS: Good Health Practices Scale
HR: heart rate
HRV: heart rate variability
HRVBF: heart rate variability biofeedback
iKT: integrated knowledge translation
iPREP: International Performance Resilience and Efficiency Program
LEAPS: Lam Employment Absence and Productivity Scale
LMS: learning management system
PASAT: Paced Auditory Serial Addition Test
PCL-5: PTSD Checklist (DSM-5)
PHQ-8: Personal Health Questionnaire-8 Item
PNS: parasympathetic nervous system
PSP: public safety personnel
PSQ: Police Stress Questionnaire
PSS: Perceived Stress Scale
PTQ: Perseverative Thinking Questionnaire
PTSD: posttraumatic stress disorder
PTSI: posttraumatic stress injury
RSA: respiratory sinus arrhythmia
RSA-33: Resilience Scale for Adults-33 Item
SDS: Sheehan Disability Scale
SNS: sympathetic nervous system
UB-PSWQ: Ultra Brief-Penn State Worry Questionnaire
UB-RRS: Ultra Brief-Rumination Response Styles
WBSI: White Bear Suppression Inventory
WGDS: Workplace Gender Discrimination Scale
WHODAS 2.0: World Health Organization Disability Assessment Scale 2.0
